### Sample size computation

A non-inferiority hypothesis test was adopted in this study. Based on a previous retrospective study that showed that the mean ± standard deviation of the estimated blood loss during the operation in the CTA group and non-CTA group was 72.5 ± 66.4 ml and 93.5 ± 88.4 ml [15], respectively, we calculate that 382 patients were required to participate in this study (191 patients in the experimental group and 191patients in the control group) providing a significant level of *α* = 0.05 using a one-sided two-sample *t* test, a power of 1-β = 80%, and a maximum dropout rate of approximately 10%. The sample size computation was performed using PASS 11 (NCSS, LLC. Kaysville, UT, USA).

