Some studies have already declared the usefulness of the application of CT angiography before surgery. Iino et al. demonstrated that preoperative acquisition of perigastric vessel information might contribute to the safe dissection of lymph nodes during laparoscopic gastrectomy [12]. According to the study of Mu et al. [14], the surgeon can have a good acquaintance of celiac artery on its origin, course and variation and vascular calcifications for the patients that underwent gastrectomy with the help of 64-MSCTA, and it is also recommended that CTA should be a preoperative conventional procedure in gastric cancer patients.

Based on a retrospective propensity score matching study [15], we proposed a novel classification of the perigastric vessels according to the processing of CTA images, which indicates that utilizing CTA can further improve short-term clinical recovery course including more harvest of lymph nodes and less estimated blood loss and operation time, compared with patients who received abdominal enhanced CT without CTA, especially for patients whose BMI ≥ 25 kg/m^2^. To the best of our knowledge, few multicentre randomized controlled prospective studies have focused on the application of CTA for patients who are diagnosed with gastric cancer before undergoing laparoscopic gastrectomy.

For further research, we planned this multicentre controlled trial, which is named after GISSG 20–01, to verify whether the use of CTA can improve the short- and long-term clinical outcomes of patients who undergo laparoscopic or robotic gastrectomy.

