### Randomization

In this trial, eligible patients will be randomly assigned to either the CTA group or the non-CTA group in a 1:1 ratio. A central dynamic, stratified strategy was adopted for the aim of randomization. The sequence of randomization was generated by a certain doctor who was independent of this trial using the method of Pocock-Simon minimization by SAS 9.3 (SAS Institute Inc., Cary, NC, USA) and stratified by participating site (14 hospitals) and surgical approach (laparoscopic or robotic). The above information provided by the participating centres was submitted to the data centre at the Department of Gastrointestinal Surgery, Affiliated Hospital of Qingdao University, China, where central randomization was executed. Consequently, the allocation information will then be sent to each participating site. The allocation procedure was not blinded to the investigators or patients but was masked for data collection and analysis.

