### Data collection and analysis

An a priori designed and coincident case report form (CRF) will be used to record the information required by the study, such as baseline characteristics, laboratory data, perioperative clinical recovery course and long-term oncological outcomes, and a designated clinical investigator is responsible for the collection of data at each centre. Moreover, to keep track of changes to the data, any correction to the raw data requires signing the date and the investigator’s name. A monthly data check that includes data summarized by each centre, abnormal data and delayed data in progress tracking is required during the trial period.

Continuous variables will be presented as the mean ± standard deviation, while classification variables will be described as numbers (*N*) and percentages (%) to express the difference between two groups. To compare continuous variables for the two groups, Student’s *t* tests or Mann–Whitney *U* tests will be performed, and categorical variables will use the *χ*^2^ test or Fisher’s exact test. OS and DFS, defined as the time from surgery to death and the time from surgery to tumour recurrence or death from any cause, respectively, will be assessed by the Kaplan–Meier method with the log-rank test to analyse the differences in the survival curves. A Cox proportional hazards regression model with a 95% confidence interval will be used to perform univariate and multivariate analyses. Subgroup analyses will also be performed, with participants stratified by BMI (25.0 to 29.9 kg/m^2^, ≥ 30 kg/m^2^), to verify the effect of CTA on short-term and long-term clinical outcomes in overweight and obesity patients between CTA group and non-CTA group. For missing data, multiple imputation was used to obtain complete datasets. A *P* value less than 0.05 will be considered statistically significant. The 25th version of SPSS (SPSS Inc., Chicago, IL, USA) will be used to analyse the data.

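### The sample size section calls the primary hypothesis non-inferiority, but the aim, the effect input and the 382 patients are those of a one-sided superiority test

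*Protocol article*

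**What the plan says.** All places are in the protocol article.

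- *Sample size computation* opens with the hypothesis type: "A non-inferiority hypothesis test was adopted in this study". No margin follows, there or elsewhere in the article.
- The only effect input comes from the group's earlier retrospective study. Mean ± SD blood loss in the "CTA group and non-CTA group was 72.5 ± 66.4 ml and 93.5 ± 88.4 ml" respectively.
- The test is fixed by "providing a significant level of *α* = 0.05 using a one-sided two-sample *t* test", with 80% power and a dropout allowance of about 10%. The result is "we calculate that 382 patients were required to participate in this study", 191 per arm.
- *Background and rationale* gives the purpose as "to verify whether the use of CTA can improve the short- and long-term clinical outcomes". The *Discussion* argues that CTA could reduce arterial damage and bleeding during lymph node dissection.
- *Data collection and analysis* plans t or Mann–Whitney tests for continuous variables. A P "value less than 0.05 will be considered statistically significant". It mentions no margin or confidence-bound rule, and does not say whether the test is one- or two-sided.

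**The concern.** The hypothesis type fixes the null value and therefore what the trial may conclude about its primary endpoint. Here the declared type disagrees with the aim and with the effect size used to set the sample size.

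The consequence would be felt if the blood loss comparison misses significance. A published non-inferiority label with no fixed margin would let a margin be chosen after the data are seen, and CTA be reported as not inferior. CTA is an added examination whose rationale is less bleeding, so that conclusion would not answer the trial's question. The trial is open-label, and *Strengths and limitations* concedes that surgeon subjectivity may affect results. That is a further reason to fix the claim in advance.

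**Working it through.** **Inputs** (*Sample size computation*; 1:1 allocation from *Randomization*): means 72.5 and 93.5 ml, difference 21.0 ml; SDs 66.4 and 88.4 ml; one-sided alpha 0.05; power 80%; dropout about 10%.

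**Step 1. Reproduce 382 as superiority with margin zero.**

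n per arm = (z₀.₉₅ + z₀.₈₀)² × (SD₁² + SD₂²) / difference²

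- Sum of variances: 66.4² + 88.4² = 4408.96 + 7814.56 = 12223.52
- (1.645 + 0.842)² = 6.183, using unrounded quantiles
- n = 6.183 × 12223.52 / 441 = 171.4 per arm
- Dropout: 171.4 / 0.9 = 190.4, rounded up to 191; 2 × 191 = 382

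A noncentral t calculation gives 173 per arm: 173 × 1.1 = 190.3, rounded up to 191, or 173 / 0.9 = 192.2, rounded up to 193. The article does not say how rounding and dropout were handled, but every route gives 190 to 193 per arm. The planned size is reproduced.

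**Step 2. Non-inferiority with the stated means as the truth.** The distance to the null becomes 21 + M, where M is the margin in ml:

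n per arm = 6.183 × 12223.52 / (21 + M)²

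| Margin M | Evaluable per arm | Per arm after /0.9 |
|---|---|---|
| 0 (superiority) | 172 | 192 |
| 1 ml | 157 | 175 |
| 5 ml | 112 | 125 |
| 10 ml | 79 | 88 |
| 21 ml | 43 | 48 |

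Any positive margin gives a number below the planned one, and well below it from about 5 ml upward.

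**Step 3. Non-inferiority with a true difference of zero.** The distance is M alone:

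- M = 10 ml: 6.183 × 12223.52 / 100 → 756 per arm
- M = 20 ml: / 400 → 189 per arm
- M = 21 ml: / 441 → 172 per arm

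So a margin near 21 ml with no true difference also gives the planned size. The article states neither assumption. That margin would tolerate CTA being worse by as much as the whole expected benefit.

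**Step 4. Sidedness.** The design is one-sided at 0.05; the analysis section gives 0.05 without a side. If two-sided:

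- Required n = (1.960 + 0.842)² × 12223.52 / 441 → 218 per arm (219 by noncentral t). After dividing by 0.9 this is 243 to 244 per arm, 486 to 488 in total.
- Power with 172 evaluable per arm: SE = √(12223.52 / 172) = 8.43 ml; 21 / 8.43 − 1.960 = 0.53; power about 70%.
- Power with all 191 per arm: SE = √(12223.52 / 191) = 8.00 ml; 21 / 8.00 − 1.960 = 0.665; power 74 to 75%.

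**The case against.** **The hypothesis can be tested.** A reader might infer from the missing margin that the primary hypothesis is untestable. The document does not support this: it names one primary endpoint and a one-sided two-sample t test at 0.05, which can be run as written. Only a non-inferiority null with a non-zero margin lacks a value. With margin zero, the test is the one that was sized.

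**The number alone does not identify the hypothesis.** This stands: Step 3 shows that 382 also fits a 21 ml margin with zero true difference. The superiority reading rests on the number together with the stated 21 ml benefit and the stated aim.

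**The margin may be in the full protocol.** The article condenses protocol version 1.3, which is not shown, so the missing margin is weak evidence by itself. But no positive margin, wherever stated, would reconcile 382 with the means given here.

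**The analysis section is generic.** Its 0.05 rule covers all variables, and a confidence-bound rule could sit in an analysis plan. This is fair; that section is supporting evidence only. The abstract and *Objective* are also neutral on direction, speaking of changing or exploring outcomes, but neither points to non-inferiority.

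**No misuse is planned.** Nothing in the document proposes a claim of non-inferiority after a failed superiority test. The wording leaves room for one, and no more should be inferred.

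**Conclusion.** The concern holds as a mislabelled primary hypothesis. The aim, the sole effect input and the sample size agree with each other and with one-sided superiority at margin zero: 171 to 173 evaluable per arm, about 191 with dropout. Only the non-inferiority sentence disagrees. Non-inferiority fits 382 only under two assumptions that the article does not make.

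A reader might go further and conclude that the sample size is wrong. It is not: the arithmetic is sound for the one-sided test described. Its adequacy is conditional on that test being the one used. If the primary analysis is two-sided at 0.05, power is about 70% with 172 evaluable per arm (74 to 75% with all 191), not 80%. These figures rest on the retrospective means and SDs and on a t test comparison.

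**What to change.** 1. In *Sample size computation*, replace the non-inferiority sentence with a superiority hypothesis: mean intraoperative blood loss is lower with CTA, null difference 0, planning difference 21 ml.
2. State that a non-significant result will not be reported as non-inferiority.
3. In *Data collection and analysis*, state that the primary test is one-sided at 0.05, as sized. If a two-sided 0.05 test is meant, keep 382 and restate the power as about 70% with 172 evaluable per arm (about 74% with all 191).
4. If the sponsor does intend non-inferiority, give instead the margin with its justification, the assumed true difference and a matching calculation.

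Cost: a short text change with no change in the number of patients under items 1 to 3. It is not merely editorial. *Participant selection* requires a formal amendment for major modifications such as a change to the study design, with agreement of the study group and ethics approval. It should be done before the outcome data are analysed, because afterwards the choice of hypothesis would no longer be credible.

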### Outcomes

The primary endpoint of this trial is the volume of blood loss that occurs during the surgery. The second primary endpoints are as follows: (1) the harvested number of lymph nodes is defined as the dissection number of lymph nodes through the standard extent of lymph node dissection, which is conducted with the principal of lymph node dissection guided by the 2018 version of Japanese Gastric Cancer Treatment Guidelines; (2) postoperative recovery course, which refers to the items of time to first ambulation, flatus, liquid diet and so on; (3) hospitalization costs are defined as the total expenses during hospitalization brought on by treatment and care; (4) length of hospitalization days, which is defined as from the day of surgery to the day of discharge; and (5) the severity of postoperative complications, which include anastomotic leakage, pancreatic fistula, and pulmonary or abdominal infection, and are evaluated by the classification of Clavien–Dindo [16]. Complications were recorded when they were worse than grade II. Moreover, 3-year OS (overall survival) and 3-year DFS (disease-free survival) will also be followed up and recorded.

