### Trial design

The GISSG20–01 study is a multicentre, prospective, open-label clinical study in which patients who meet the inclusion criteria will be randomly assigned to an experimental group (CTA group) and a control group (non-CTA group) in a 1:1 ratio. In addition to the standard examinations in both groups, the patients in the CTA group will receive upper abdomen enhanced CT and CT angiography while the non-CTA group will receive upper abdomen enhanced CT only.

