### Participant selection

Patients who are diagnosed with gastric cancer and plan to undergo laparoscopic or robotic gastrectomy will be enrolled from the 14 centres listed in Table 1. The launching conference was held online and was used to inform the participating staff about the details of the GISSG 20–01 trial. To obtain enough enrolled patients, all gastrointestinal surgeons in the participating centres were informed that the clinical trial was recruiting, and hospitalized patients were given the details about the trial for the purpose of enrolment. There are usually four ways to recruit patients: inpatients of gastrointestinal surgery, outpatients of gastrointestinal surgery, displaying poster at outpatient clinic or releasing recruitment information on the Internet. The enrolment of the first patient was started in November 2020, while it is anticipated that the deadline for the recruitment of the patients will be in November 2021. In the end, 382 patients who meet the inclusion criteria will be included in this trial. The study protocol and informed consent form were approved by the ethics review board of all research hospitals before the enrolment of any patients. Well-trained research doctors are responsible for introducing the main contents of the study to the patients and obtaining informed consent from patients who voluntarily participate in the trial in each centre. The flowchart that demonstrates the process of enrolment of the patients is shown in Fig. 1. The study protocol was revised to version 1.3 in December 2020. Any major modifications to the study protocol that may have a significant influence on the execution of the trial, including changes in the inclusion or exclusion criteria, number of samples or the study design, will require a formal amendment to the protocol. Such major modifications will be agreed up on by the GISSG (Gastrointestinal Surgery Study Group) and approved by the ethics review board. Protocol modifications are transmitted through the research meeting, and the electronic manual is distributed to the sub-centre researchers. An integral checklist of items in accordance with SPIRIT (Standardized Protocol Items: Recommendations for Intervention Trials) (2013 version) was supplied in additional file 1.

**Table 1 Tab1:** The 14 participating centres

Number	Centre	Department	Investigator
01	The Affiliated Hospital of Qingdao University	Gastrointestinal Surgery	[name]

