A preoperative mandatory abdominal enhanced CT scan will be performed in both the experimental group and the control group to evaluate the clinical stage of the tumour. Moreover, compared with the non-CTA group, the patients in the CTA group will be asked to undergo the CTA examination once they are randomly assigned to the experimental group. To improve adherence to the intervention protocols, the patients will be fully informed of the potential short-term clinical recovery course and long-term oncological effects. Regular research meetings are held to provide relevant study guidance for researchers. For the researchers, there are mainly three ways to enhance adherence to intervention protocols including researcher training, regular researcher meetings and regular visits to the sub-centres. Abdominal enhanced CT will be performed using a 64-detector row CT scanner in this study, while the type of CT equipment is according to what is available in each participating centre. The procedure of the abdominal enhanced CT was set to ensure the same standard for the reconstruction of the perigastric arteries across centres. Fasting no less than 8 h before the examination is required, and an injection of 10 mg anisodamine 10 min before the examination is necessary for the purpose of reducing gastric distention and motility. Nonionic iodinated contrast material will be used as the contrast agent, injected at a speed of 4.0 ml/s by an automatic injector, and its volume is based on the weight of the patient; for example, for patients weighing 60 kg or less, the lower limit is 120 ml, and for patients weighing more than 75 kg, the upper limit is 150 ml.

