**Fig. 2 Fig2:**
[figure not shown]
The items of enrolment, interventions and assessments in the flowchart. The symbol of × represent that the program needs to be collected. −1, 2 weeks before operation; 0, perioperation; 1, postoperative adjuvant chemotherapy time; follow-up 2~10 refers to time points that listed in the following: 2, 1 months after surgery; 3, 3 months after surgery; 4, 6 months after surgery; 5, 9 months after surgery; 6, 12 months after surgery; 7, 18 months after surgery; 8, 24 months after surgery; 9, 30 months after surgery; 10, 36 months after surgery

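### The cost endpoint omits any CTA billed between randomisation and admission, and the stay endpoint is postoperative stay under a broader name

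*Protocol article*

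**What the plan says.** The Outcomes section of the protocol article defines two resource endpoints among its secondary outcomes. For cost: "hospitalization costs are defined as the total expenses during hospitalization brought on by treatment and care". For stay: "length of hospitalization days, which is defined as from the day of surgery to the day of discharge".

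The Trial design section states the contrast between arms: "the patients in the CTA group will receive upper abdomen enhanced CT and CT angiography while the non-CTA group will receive upper abdomen enhanced CT" (the control arm has nothing further). The Interventions and CTA protocol section gives the timing: "the patients in the CTA group will be asked to undergo the CTA examination once they are randomly assigned to the experimental group". The same section makes the enhanced CT common to both arms: "A preoperative mandatory abdominal enhanced CT scan will be performed in both the experimental group and the control group".

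The Participant selection section lists the recruitment routes, which include "inpatients of gastrointestinal surgery, outpatients of gastrointestinal surgery, displaying poster at outpatient clinic". The legend of Fig. 2 places the preoperative assessment point two weeks before the operation.

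**The concern.** The trial asks what happens when an extra examination is added before surgery. A cost comparison for such an add-on should contain the price of the add-on. The cost window here is tied to the hospital stay, while the intervention is tied to randomisation, and the two need not coincide for a patient recruited as an outpatient. If the scan is done and billed before admission, the endpoint records whatever CTA saves in hospital but not what CTA itself costs. The control arm has no matching charge to lose. An error of this kind does not shrink as the sample grows, and balancing the arms by site does not remove it, because it arises within each site.

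The stay endpoint raises a milder form of the same question. Its name suggests the whole hospital stay, but it starts on the day of surgery, after the CTA has been done. A reader of the results could take it as evidence on total stay, which it is not.

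**Working it through.** **Figures available.** The document gives no CTA price, no mean or SD for cost or stay, no admission-to-surgery interval, and no share of CTAs done before admission. Its one computed figure is the sample size for blood loss. That figure reproduces closely:

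- SD = √((66.4² + 88.4²)/2) = 78.18 ml; difference = 93.5 − 72.5 = 21.0 ml.
- One-sided α = 0.05 and 80% power give 172 per arm.
- 172/0.90 = 191.1, rounded up to 192 per arm, or 384 in total, against 382 stated.

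Nothing in that calculation involves cost or stay, so this point does not touch it.

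**Cost: the passages in time order.**

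1. Recruitment and randomisation can take place while the patient is an outpatient (Participant selection).
2. CTA is requested after assignment, in one arm only (Interventions and CTA protocol; Trial design).
3. The cost count covers expenses within the hospitalization (Outcomes).
4. A CTA between steps 1 and 3 is therefore excluded by the rule as written. A CTA after admission is inside the window.

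**Cost: direction and form of the bias.** Let C be the full CTA charge (acquisition, contrast, reconstruction). Let f be the share of CTA-arm patients whose CTA is billed before admission. Let S be the mean saving in other hospital costs due to CTA.

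- True difference, CTA minus control: C − S.
- Recorded difference: (1 − f)C − S.
- Bias, recorded minus true: −fC. It is 0 at f = 0 and −C at f = 1, so it never goes against CTA.
- CTA appears to save money while in truth costing more whenever (1 − f)C < S < C. This interval is empty at f = 0 and widens as f rises.

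The staging CT does not alter this. Both arms have it, so leaving it out or counting it has no systematic effect on the difference. It does bear on the size of C. The document does not say whether CTA is a separate acquisition or is reconstructed from the shared scan, so C may be a full examination or mainly reconstruction and reading.

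**Stay.** Let d be the mean number of preoperative inpatient days that CTA adds.

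- Difference in total stay = difference in postoperative stay + d.
- The endpoint measures the first term correctly and is silent on d. The document gives no value for d, and d may be zero.

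**The case against.** **On cost.** The definition refers to the total of expenses during the hospital stay and is not confined to the postoperative period, so a CTA done during the index admission is naturally included. The recruitment routes say where patients are found, not where they are scanned or billed, and the same section also mentions informing hospitalized patients. The Fig. 2 legend marks an assessment point; it does not schedule the CTA or the admission. The article condenses a fuller protocol and a case report form that are not shown, and itemised billing rules may sit there.

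Most of this stands, and it limits the point to CTAs billed before admission. It does not remove the point. The article states a window, and that window excludes such a CTA. The remedy changes a stated rule; it does not ask for detail that an article would normally leave out.

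**On stay.** The window is explicit and identical in both arms. It suits the aim of describing recovery and the discharge criteria under Postoperative care. This stands in full: the definition is sound, and only the name and the lack of a companion measure remain.

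**Stronger readings a reader might infer.**

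- That even an inpatient CTA is left out, because a diagnostic scan is not treatment or care, or because cost should share the stay endpoint's start on the day of surgery. The first strains the wording. The second carries a start date from one separately defined endpoint to another.
- That CTA lengthens the preoperative stay. No passage says that CTA delays surgery, adds inpatient days or requires waiting for a reading, and both arms already have a preoperative enhanced CT.

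**Conclusion.** The point holds in a limited form. The cost definition leaves out any CTA billed after randomisation and before admission. Such an omission can occur only in the CTA arm and can only favour it. Its size is f × C, between zero and the full CTA charge per patient. It cannot be computed from the document, and it is zero if all CTAs are done during the index admission. The possibility rests on outpatient recruitment combined with CTA after assignment; the document does not state where CTA is performed or billed.

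The stay endpoint is a valid measure of postoperative stay with a name that promises more. It cannot show preoperative days that CTA might add, and nothing in the document says that it adds any.

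A reader might conclude that both endpoints are tilted towards CTA. The document does not support that: for cost the tilt is possible but not established, and for stay the measure is the same in both arms and correct for what it covers. The matter is worth correcting because the remedy is cheap and a claim of saving or cost neutrality would depend on it. It does not affect the primary endpoint or the sample size of 382.

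**What to change.** Define cost as all charges from randomisation to discharge, and state that this includes CTA acquisition, contrast and reconstruction whether billed as outpatient or inpatient. Starting at randomisation gives both arms the same origin and makes the place of the scan irrelevant. Charges before randomisation are left out of both arms alike.

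Keep the surgery-to-discharge measure, label it postoperative stay, and report total stay by arm beside it. Measured from admission to discharge, total stay counts hospital days. Measured from randomisation, it would also show any delay to surgery. The plan should say which is used.

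Settle the wording before cost or stay is compared between arms. The change costs a few extra billing and date fields that hospitals would ordinarily hold, plus a rewording of two endpoints. The one downside is that the cost result for CTA may become less favourable; if every CTA was done in the index admission, counting it explicitly changes nothing on that account.
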